### 6.2 Efficacy Analysis

Tabular and graphical descriptive statistical methods will be used to characterize the study group at baseline in terms of demographic and clinical measures. For each arm of the study, the proportion of participants whose NAS is reduced by at least 2 points ( $\pi$ ) will be estimated

along with corresponding 95% confidence intervals. Point and interval estimates of the distributions of NAS, ALT, fibrosis score, HOMAr, and at baseline will also be tabulated.

The primary null hypothesis, that the proportion of participants whose NAS is reduced by at least 2 points ( $H_{01}: \pi_0 = \pi_1 = \pi_2$ ) will be tested against the general alternative hypothesis,  $H_{a1}$  that response differs in at least one treatment arm via a chi-square test for association with  $\alpha = 0.05$ . If  $H_{01}$  is rejected, then pairwise comparisons of the arms will be examined using a sequentially rejective test procedure (Holm, 1979). Computation of these results for the ITT analysis will comprise the main results of this study.

A per protocol analysis will also be performed. Participants will be included in this analysis if they took at least 80% of the medication.

The null hypotheses of no difference among treatment arms will be tested for the secondary outcomes. For dichotomous outcomes (secondary outcomes 2 and 3 above), the methods described for testing the primary hypothesis will be used. Change in HOMAr will be compared among the groups using either parametric or non-parametric analysis of variance, as appropriate. The null hypothesis of no treatment differences among the three groups for continuous outcomes will be tested using analysis of variance. Post-hoc tests to identify pairwise differences should the null hypothesis be rejected will control for multiple comparisons.

To maximize statistical power, there will not be an adjustment for the multiple outcomes since the results will be used to guide the design of a proposed phase III study.

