### **6.3 Power considerations**

The sample size is determined by the size of the effect (i.e., the percentage of participants whose NAS is reduced by at least 2 points) of silymarin (comparing participants in the placebo arm to those taking silymarin), the type I and II error rates, and the dose response of silymarin.

Assuming that the NAS will be reduced by at least 2 points in 15% of participants in the placebo arm (most likely to occur due to biopsy sampling error or misclassification or because of the lifestyle change) versus 47.5% of participants taking silymarin (40% in the lower dose and 55% in the higher dose group) then with 40 participants in each group will provide 83% power to reject the null hypothesis at  $\alpha=0.05$ . For participants who drop out, the last observation carried forward method will be used to impute the final outcome if a follow-up liver biopsy is available. Otherwise the drop out would be considered treatment failures. Thus no over-recruitment to account for loss to follow-up is necessary.

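### Holm after a significant three-arm overall test is valid but needlessly conservative: it costs about 8 points of power for 420 mg versus placebo that the nominal 5% familywise guarantee does not require

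*Protocol*

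**What the plan says.** Protocol Section 6.2 (Efficacy Analysis) sets the primary null hypothesis as equality of the three arms' proportions with a NAS reduction of at least 2 points. It is tested "via a chi-square test for association with" a significance level of 0.05. If it is rejected, "then pairwise comparisons of the arms will be examined using a sequentially rejective test procedure (Holm, 1979"). The ITT version of these results is named as the study's main result. The same section waives multiplicity adjustment across endpoints on grounds of power: "To maximize statistical power, there will not be an adjustment for the multiple outcomes".

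Section 6.3 (Power considerations) assumes response in "15% of participants in the placebo arm" and "47.5% of participants taking silymarin" ("40% in the lower dose and 55% in the higher dose group"), and states that these rates "with 40 participants in each group will provide 83% power to reject the null hypothesis at" 0.05. Participants who drop out without a follow-up biopsy count against response: "Otherwise the drop out would be considered treatment failures". Section 6.3 gives no power for either dose against placebo.

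**The concern.** Two layers of protection apply to the same family of comparisons. The overall test must first reject at 0.05. Holm then requires the smallest of three p-values to reach 0.05/3, the second 0.05/2 and the third 0.05. In a three-arm trial the first layer alone already gives strong familywise control at nominal 5% if each pair is then tested at 0.05.

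The second layer falls mainly on the weaker dose. Under the planned rates, 700 mg versus placebo usually gives the smallest p-value and 420 mg versus placebo the second, so 420 mg must typically reach 0.025 and not 0.05. The 420 mg arm was chosen to see whether lower exposure gives a different response, so loss of power there weakens part of what the design is meant to show. Section 6.2 gives up adjustment across endpoints for the sake of power, so an unneeded loss within the primary endpoint runs against the plan's own stated aim.

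**Working it through.** **Inputs.** Response rates 15%, 40% and 55% and 40 participants per arm (Section 6.3); alpha 0.05, overall chi-square, then Holm (Section 6.2). My readings: the pairwise tests are uncorrected Pearson chi-squares, and the Holm family is all three pairs, which is what pairwise comparisons of three arms naturally means.

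**The plan's own figure.** The 83% is reproduced by a two-group calculation of 15% against the pooled 47.5%. With mean rate 0.3125 and difference d = 0.325:

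- n0 = [1.96·√(2·0.3125·0.6875) + 0.954·√(0.15·0.85 + 0.475·0.525)]² / 0.325² = 33.1
- with continuity correction, n = (n0/4)·[1 + √(1 + 4/(n0·d))]² = 39.04, rounded up to 40 per group

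It is not the power of the planned three-arm test. For that test the mean rate is 0.3667 and the noncentrality is 40·(0.2167² + 0.0333² + 0.1833²)/(0.3667·0.6333) = 14.07. On 2 degrees of freedom this gives 92.9%; exact enumeration gives 95.3%. The stated 83% therefore says nothing about the pairwise step.

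**Why Holm is redundant.** Call the pairwise nulls H1 (placebo = 420 mg), H2 (placebo = 700 mg) and H3 (420 mg = 700 mg). If any two are true, all three rates are equal, so every intersection of two or three of them is the global null.

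- All three true: a false pairwise claim requires the overall test to reject, which has probability 0.05 (nominal).
- Exactly one true: only that one can be falsely rejected, and it is tested at 0.05.
- Exactly two true: impossible.

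The overall test at 0.05 followed by each pair at 0.05 is therefore a closed test. The argument depends on there being exactly three arms.

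**Power.** All 41³ = 68,921 outcomes were enumerated and weighted by the product of three binomial(40, p) probabilities. Both columns require a significant overall test.

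| 15/40/55%, 40 per arm | Holm | Pairs at 0.05 | Loss (points) |
|---|---|---|---|
| 420 mg vs placebo | 63.5% | 71.7% | about 8 |
| 700 mg vs placebo | 93.7% | 94.9% | about 1 |
| Both doses vs placebo | 62.7% | 71.4% | about 9 |
| 420 mg vs 700 mg | 23.6% | 28.7% | about 5 |
| Overall significant, no pair significant | 0.8% | essentially 0 | – |

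For 420 mg versus placebo the loss varies with the pairwise statistic: 6.8 points with Wald tests (66.2% vs 73.0%), 10.2 with Yates (53.0% vs 63.2%) and 10.4 with Fisher (53.6% vs 64.0%).

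**Sensitivity.** Assume 20% dropout without a biopsy, scored as failure; the 20% is an assumption, as the protocol gives no rate. The rates become 0.8 × (15, 40, 55) = 12/32/44%. Power for 420 mg is then 47.3% vs 57.5%, and for both doses 45.3% vs 56.6%. With smaller assumed effects (15/30/40%), power for 420 mg is 24.4% vs 32.6%, and a significant overall test without a significant pair occurs in 3.0% of trials under Holm.

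**Realised familywise error, same enumeration.**

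| True rates (placebo/420/700) | Holm | Pairs at 0.05 |
|---|---|---|
| 15/15/15% | 3.7% | 4.6% |
| 30/30/30% | 4.0% | 5.0% |
| 15/15/40% | 3.1% | 5.1% |
| 15/40/40% | 3.3% | 5.1% |
| 15/47.5/47.5% | 4.1% | 5.6% |
| 15/15/90% | 5.35% | 5.35% |

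Over a grid of rates from 5% to 95% the worst case is 5.87% for both procedures. The excess over 5% comes from the discreteness of the chi-square test and not from multiplicity.

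**The case against.** The plan is valid as written. Holm after the overall test controls familywise error, Section 6.2 is internally consistent, and no stated power figure depends on the pairwise step. All of that stands, so a reader should not infer that type I error is inflated or that the 83% is undermined by this point.

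A reader might also infer that Holm buys no error control at all. The figures do not support that. The nominal guarantee and the worst case are the same, but in plausible settings Holm lowers the realised error, for example 3.1% against 5.1% at 15/15/40%. The 15/15/90% row shows equality only because the extreme arm always carries Holm to its last step at 0.05, and no rate near 90% is assumed in the protocol.

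A reader might further infer that the phase III dose rests on these tests. The protocol says only that the results will guide phase III design. It also provides response rates with confidence intervals by arm, toxicity rates by dose, and exposure-response modelling, and it states no rule tying dose choice to pairwise significance.

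Finally, the size of the Holm family is not spelled out. If it were only the two placebo comparisons, Holm after the overall test would give 71.7% for 420 mg, 94.8% for 700 mg and 71.3% for both, and almost nothing would be lost. That is arithmetically right, but it is not the natural reading of pairwise comparisons among three arms, and it would leave the two doses uncompared.

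**Conclusion.** The point holds as an efficiency improvement to a valid plan. Holm is not needed for nominal 5% familywise control in this three-arm design. At the protocol's planning rates it costs about 8 points of power for 420 mg versus placebo, about 9 for showing both doses better than placebo, and about 1 for 700 mg versus placebo. It also permits a significant overall result with no significant pair in 0.8% of trials. The sizes rest on uncorrected chi-square pairs, a Holm family of three, 40 analysed per arm and the 15/40/55% rates; across other pairwise statistics the 420 mg loss runs from 6.8 to 10.4 points. What is given up by dropping Holm is conservatism below the nominal level, not the guarantee itself.

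**What to change.** In Section 6.2, replace the Holm sentence with: if the overall chi-square test is significant at 0.05, each of the three pairwise comparisons is tested at two-sided 0.05; with three arms this is a closed testing procedure controlling the familywise error at 5%. Name the pairwise statistic in the same place.

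The cost is one sentence, with no change to sample size, data collection or timing. Realised familywise error moves up to about the nominal 5% in some configurations (3.7% to 4.6% with all rates at 15%; 3.1% to 5.1% at 15/15/40%). The change should be made before unmasking. The sentence must be revisited if the number of arms ever changes, because the argument does not extend beyond three. If the sponsor prefers to keep Holm for its extra conservatism, the protocol should state the family of comparisons and acknowledge the power given up.

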In a trial designed to explore the efficacy of a therapy, it is important to control for potential confounding and interacting factors. Therefore, only patients who achieve and maintain a stable weight and lifestyle, to minimize the effect of such factors as change in weight or activity levels during the trial, will be enrolled. A weight range of +/- 10% change during the lead-in phase was chosen empirically; a weight change greater than this would be expected to be clinically significant and may affect (either improve or exacerbate) steatohepatitis, and thus function as a confounder. Among people with diabetes, the ideal patient population would be type 2 patients with insulin resistance who are not treated with any pharmacological agents. However, such stringent criteria would narrow the available subject population severely. As a result, patients with diabetes who are either diet controlled or who are receiving secretagogues with or without insulin will be enrolled. Therapy with secretagogues has not been suspected to mitigate the development of steatosis or the onset of steatohepatitis. Additionally, none of these medications is known to inhibit phase II metabolic processes and are thus less likely to influence silymarin disposition in humans. Similarly, although some secretagogues are metabolized by CYP isoforms, it is not anticipated that even the higher doses of silymarin used in this study will generate micromolar concentrations associated with CYP inhibition. In this phase II trial, the placebo control will allow the research team to discern the treatment effect attributable to silymarin, and thus support the study's validity as a pivotal trial and advancement to phase III studies.

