### **2.2 Secondary Objectives:**

1. To compare NAS before and after therapy
2. To characterize changes in ALT during silymarin therapy
3. To compare HOMAr before and after silymarin therapy
4. To explore relationships between silymarin therapy and serum biomarkers (oxidative stress, apoptosis, and fibrogenesis)

5. To characterize the population pharmacokinetics and pharmacodynamics of silymarin isomers including, silibinin A and B, isosilibinin A and B, silicristin, and silidianin following administration of silymarin to subjects with NASH.

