### Secondary

- Improvement by at least 1 point in histology (NAS) after therapy
- ALT or AST  $\leq$  45 IU/L (approximate normal range) or with greater than 50% reduction in ALT or AST to a value less than 65 IU/L (approximately 1.5 times the upper limit of normal) after therapy
- Insulin resistance measured by HOMAr.

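### The HOMAr comparison in section 6.2 is valid but inefficient, because it uses neither baseline HOMAr nor the stratification factors; an outcome number and the handling of insulin users also need small corrections

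*Protocol*

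**What the plan says.** Section 2.3 lists three secondary endpoints in this order: "Improvement by at least 1 point in histology (NAS) after therapy"; an ALT/AST response, defined by a near-normal value or alternatively "with greater than 50% reduction in ALT or AST to a value less than 65 IU/L"; and "Insulin resistance measured by HOMAr". The first two are yes/no outcomes and the third is continuous. In the numbered secondary objectives of section 2.2, item 3 is also HOMAr: "To compare HOMAr before and after silymarin therapy".

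Section 6.2 tests the primary hypothesis "via a chi-square test for association with" a significance level of 0.05, with Holm pairwise comparisons if it is rejected. For the secondary outcomes it says: "For dichotomous outcomes (secondary outcomes 2 and 3 above), the methods described for testing the primary hypothesis will be used". The next sentence reads: "Change in HOMAr will be compared among the groups using either parametric or non-parametric analysis of variance, as appropriate". Neither baseline HOMAr nor any other covariate is mentioned.

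Fasting glucose and insulin are taken at the randomisation visit and HOMAr is calculated from them (Baseline/Randomization Procedures). Allocation is within strata of site and diabetes status (section 6.0, Randomization). On diabetes treatment, the Rationale for Subject Population states that "patients with diabetes who are either diet controlled or who are receiving secretagogues with or without insulin will be enrolled". Insulin is not among the agents listed in the exclusion criteria of section 3.3. The criterion on unchanged anti-diabetic agent and dose there runs only up to randomisation.

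**The concern.** The Summary names HOMAr among the specific objectives, and section 6.2 says the results will guide a phase III design. Section 6.2 also forgoes adjustment for multiple outcomes in order to keep power. Yet the method it fixes for HOMAr leaves out the baseline value, usually the strongest single predictor of the follow-up value, and the two factors that define the randomisation strata. One of these, diabetes status, bears directly on insulin resistance. With 40 participants per arm, what is at stake is avoidable imprecision in a secondary comparison.

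Two lesser matters sit beside it. The outcome numbers point the primary method at a continuous index and away from the 1-point NAS endpoint. And HOMAr is built from measured insulin in a population that may include people who inject it, with no rule on how their values are to be read.

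**Working it through.** **1. The outcome numbers.** The two lists side by side:

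| Position | Section 2.2 objective | Section 2.3 secondary endpoint | Type of endpoint in 2.3 |
|---|---|---|---|
| 1 | NAS before and after | NAS improvement of at least 1 point | yes/no |
| 2 | change in ALT | ALT/AST response | yes/no |
| 3 | HOMAr | HOMAr | continuous |

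Under either list number 3 is HOMAr. The two dichotomous endpoints of section 2.3 are numbers 1 and 2.

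**2. Precision of the change score.** The protocol states no standard deviation, effect size, correlation or power for HOMAr, so there is no figure of its own to reproduce. The inputs are:

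- 40 per arm, from section 6.3.
- The correlation rho between baseline and week 48. This is not given and is assumed here to lie between 0.3 and 0.8.
- A common standard deviation s at both times, also assumed.

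The formulas are:

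- Variance of the change score: 2(1 − rho)s².
- Residual variance after adjustment for baseline: (1 − rho²)s².
- Ratio of the first to the second: 2(1 − rho)/[(1 − rho)(1 + rho)] = 2/(1 + rho).
- Number per arm that a change-score analysis would need to match 40 with ANCOVA: 40 × 2/(1 + rho).

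| rho (assumed) | Change score, in s² | ANCOVA, in s² | Ratio | Equivalent n per arm |
|---|---|---|---|---|
| 0.3 | 1.40 | 0.91 | 1.54 | 62 |
| 0.5 | 1.00 | 0.75 | 1.33 | 53 |
| 0.7 | 0.60 | 0.51 | 1.18 | 47 |
| 0.8 | 0.40 | 0.36 | 1.11 | 44 |

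**3. What that means for power, as an illustration only.** Take assumed mean shifts of 0, 0.25 and 0.5 s in the three arms. The mean shift is 0.25 s, so the sum of squared deviations is (0.0625 + 0 + 0.0625)s² = 0.125 s². The noncentrality of the three-arm F test is 40 × 0.125 = 5, divided by the variance from the table in units of s². At alpha 0.05 the power is:

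- rho 0.3: 37% with the change score (noncentrality 5/1.40 = 3.57), 53% with ANCOVA (5/0.91 = 5.49).
- rho 0.5: 49% (5.00) and 62% (5/0.75 = 6.67).
- rho 0.7: 72% (5/0.60 = 8.33) and 80% (5/0.51 = 9.80).

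These figures cover adjustment for baseline alone. They do not measure any further effect of the log scale, diabetes status or site.

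**4. Insulin users.** The protocol's formula is glucose (mg/dL) × 0.05551 × insulin / 22.5. At a fixed glucose the index is proportional to measured insulin, so a doubling of measured insulin doubles HOMAr. With glucose 100 and insulin 10 the formula gives 100 × 0.05551 × 10/22.5 = 2.47; with insulin 20 it gives 4.93. If the assay registers injected insulin, dosing can therefore move the index without a change in insulin resistance. Nothing in the document asks for stable anti-diabetic dosing between randomisation and week 48. The Rationale for Silymarin in NASH cites a study in which need for injected insulin was itself an outcome under silymarin, so the protocol's own background allows that dosing could change differently by arm. The share of insulin users is not stated, and the size of any effect cannot be computed.

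**The case against.** The strongest reply is that nothing here is wrong in the sense of biased. A change score compared by analysis of variance is valid under randomisation, a rank-based version is allowed for, and covariates and transformation are often settled in a statistical analysis plan, which is not at hand. That it is valid stands in full. The deferral stands only in part: section 6.2 does not leave the HOMAr method open but names one, without covariates, and a better one costs nothing. It is also fair that the correlations are assumptions, and that at 0.8 the gain is only about 11%.

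On the numbering, a reader might infer that HOMAr has two incompatible analyses and that the 1-point NAS endpoint has none. The text does not support that. The governing words are those limiting the sentence to dichotomous outcomes, which cover the NAS endpoint and cannot cover an undichotomised index. The following sentence names HOMAr and gives it its own test. The numbers would even fit if the primary endpoint were counted as the first. But the sentence says secondary outcomes, so the label is still wrong.

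On insulin, a reader might infer that the HOMAr comparison is contaminated and that insulin users should be removed from it. The documents do not carry that either. No assay is described, so its response to injected insulin is an assumption. The share of users is unknown. Stratification by diabetes status, the HbA1c limit and stable treatment up to randomisation should keep any baseline distortion broadly balanced. What remains is the possibility of differential dose changes on treatment, which a supportive analysis can address.

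**Conclusion.** The HOMAr analysis in section 6.2 is valid but inefficient. If variances are equal at both times and the baseline to week-48 correlation is between 0.3 and 0.8, the change score carries about 1.54 to 1.11 times the variance of a baseline-adjusted analysis. Put differently, 40 per arm with ANCOVA does the work of about 62 to 44 per arm without it. Calling the plan mis-specified would go too far, since the loss is one of precision only.

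The outcome numbers are a plain slip with a recoverable meaning. The absence of any HOMAr provision for insulin users is a real but unquantified gap in interpretation. HOMAr is a secondary outcome, and none of this touches the primary NAS analysis.

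**What to change.** In section 6.2:

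1. Replace the comparison of change by an ANCOVA of week-48 HOMAr on the log scale, with baseline log-HOMAr, diabetes status and site as covariates and treatment arm as the factor. Arm contrasts then back-transform to ratios of geometric means.
2. Change the outcome numbers from 2 and 3 to 1 and 2.
3. Add a supportive HOMAr analysis restricted to participants not on insulin at baseline, with all participants kept in the main analysis. Do not define this subset by insulin use at week 48. That status arises after randomisation, and the study cited in the background suggests treatment may affect it, so selecting on it could undo the randomised comparison.
4. Report changes in insulin treatment during the study by arm, so that a reader can judge whether HOMAr has moved with dosing.

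The cost is a few sentences and minor programming. The baseline and week-48 glucose and insulin, the stratification factors and concurrent medications are already to be collected. The ANCOVA uses a few degrees of freedom, and the supportive analysis has a smaller sample by an amount the protocol does not allow one to state.

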### **6.3 Power considerations**

The sample size is determined by the size of the effect (i.e., the percentage of participants whose NAS is reduced by at least 2 points) of silymarin (comparing participants in the placebo arm to those taking silymarin), the type I and II error rates, and the dose response of silymarin.

Assuming that the NAS will be reduced by at least 2 points in 15% of participants in the placebo arm (most likely to occur due to biopsy sampling error or misclassification or because of the lifestyle change) versus 47.5% of participants taking silymarin (40% in the lower dose and 55% in the higher dose group) then with 40 participants in each group will provide 83% power to reject the null hypothesis at  $\alpha=0.05$ . For participants who drop out, the last observation carried forward method will be used to impute the final outcome if a follow-up liver biopsy is available. Otherwise the drop out would be considered treatment failures. Thus no over-recruitment to account for loss to follow-up is necessary.

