## 3.0 Study Design

### 3.1 Study summary

This will be a phase II, multicenter, randomized, double-masked, placebo-controlled study to assess the safety and efficacy of a standardized silymarin preparation (Legalon®) for treating patients with NASH, as defined by a NAS score of at least 4 on a baseline biopsy. Participating centers and Principal Investigators in the study are shown in Table 1. A total of 120 subjects will be enrolled at the 4 clinical centers. All subjects will be at least 18 years old, have serum AST or ALT  $>$  40 IU/L and demonstrated fatty liver. After careful evaluation, all eligible subjects will be entered into a 28-day lead-in phase in which they will undergo counseling with respect to diet, exercise, and alcohol consumption. Participants successfully completing the lead-in phase will be randomized to treatment with one of two dosages of Legalon® or a placebo. Legalon® will be administered orally thrice daily for 48-50 weeks. Subjects will be evaluated regularly for adverse events and for monitoring efficacy through blood sampling. After completing therapy, subjects will be monitored for an additional 12 weeks to measure any sustained effects of study medication and to continue to monitor for resolution of any adverse events.

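### The 83% power in Protocol section 6.3 is not the power of the planned three-arm chi-square test, which is about 93% to 95% on the stated inputs

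*Protocol*

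**What the plan says.** Section 6.2 (Efficacy Analysis) fixes the primary test. The null hypothesis is that the proportion with a NAS reduction of 2 or more points is the same in all three arms. The alternative is that "response differs in at least one treatment arm via a chi-square test for association", with alpha 0.05. Pairwise comparisons by Holm's procedure follow only if that test rejects.

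Section 6.3 (Power considerations) gives the planning assumptions:

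- Placebo: "NAS will be reduced by at least 2 points in 15% of participants in the placebo arm".
- Silymarin overall: "versus 47.5% of participants taking silymarin".
- By dose: "40% in the lower dose and 55% in the higher dose group".
- Result: "then with 40 participants in each group will provide 83% power to reject the null hypothesis", at alpha 0.05.

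The arm size agrees with section 3.1: "A total of 120 subjects will be enrolled at the 4 clinical centers", that is 3 × 40. Section 6.3 does not name the test behind the 83%. It states no dropout rate and treats a dropout without a follow-up biopsy as a failure. It makes no allowance for loss to follow-up in N.

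**The concern.** The protocol defines one primary efficacy null hypothesis, so the power to reject it should be the power of the section 6.2 test at the section 6.3 rates. Those rates are well separated, and 40 per arm should give clearly more than 83%. The text also carries a pooled silymarin rate of 47.5%, the plain average (40% + 55%)/2, which the three-arm test does not use. That raises the question of whether some other comparison was calculated.

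What is at stake is traceability. This is the only efficacy power figure in the protocol, and section 6.2 says the results will guide the design of a phase III trial. Anyone who re-plans from this section would start from a number that does not match the stated test and inputs.

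**Working it through.** **Inputs.** Rates 0.15, 0.40 and 0.55, n = 40 per arm and alpha = 0.05 (section 6.3); three-arm chi-square test, 2 df (section 6.2).

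**1. Method check on the protocol's own safety figure.** Section 6.1 gives 12% power for a three-arm chi-square test with toxicity rates 0.05, 0.10 and 0.10. The formula is λ = n Σ(p_i − p̄)² / [p̄(1 − p̄)], with power = P(noncentral χ² on 2 df with noncentrality λ > 5.991).

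- p̄ = 0.25/3 = 0.08333
- Σ(p_i − p̄)² = 0.001111 + 0.000278 + 0.000278 = 0.001667
- λ = 40 × 0.001667 / (0.08333 × 0.91667) = 0.873
- Power = 12.1%, which reproduces the stated 12%.

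**2. The efficacy figure by the same formula.**

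- p̄ = (0.15 + 0.40 + 0.55)/3 = 0.36667
- Σ(p_i − p̄)² = 0.046944 + 0.001111 + 0.033611 = 0.081667
- λ = 40 × 0.081667 / (0.36667 × 0.63333) = 14.07
- Power = **92.9%**, against 83% stated.

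Other calculations for the same test agree. Enumerating all 41³ = 68,921 outcomes gives 95.3%, simulation gives 95.3%, and the likelihood-ratio noncentrality (15.01) gives 94.4%. By the noncentral formula, 29 per arm gives 82.3% and 30 per arm gives 83.7%.

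**3. Calculations that land near 83%.**

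| Calculation | Power |
|---|---|
| 15% v 47.5%, 40 v 40, two-sided alpha 0.025 | 83.0% |
| 15% v 47.5%, 40 v 40, alpha 0.05, continuity-corrected | 84.1% |
| 15% v 40%, 40 v 40, one-sided alpha 0.05 | 81.5% |
| Three-arm test, about 18% to 19% of every arm turned into failures | about 83% |

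The first line uses the pooled-variance formula. Under the null, SE = √(0.3125 × 0.6875 × 2/40) = 0.1036. Under the alternative, SE = √[(0.1275 + 0.2494)/40] = 0.0971. Power = Φ[(0.325 − 2.241 × 0.1036)/0.0971] = Φ(0.955) = 83.0%. At alpha 0.05 the same comparison gives 89.5%. With the doses actually pooled (40 v 80) it gives 96.3%. None of these is the planned test on the stated inputs.

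**4. Effect of dropouts counted as failures.** If a fraction d of every arm has no follow-up biopsy and the assumed rates do not already allow for it, each rate becomes p(1 − d). The dropout rates here are assumptions, since the protocol gives none.

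| Assumed d | Rates | λ | Power of planned test |
|---|---|---|---|
| 0% | 0.150 / 0.400 / 0.550 | 14.07 | 92.9% |
| 10% | 0.135 / 0.360 / 0.495 | 11.97 | 88.2% |
| 20% | 0.120 / 0.320 / 0.440 | 10.09 | 81.9% |

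**5. Power of the follow-up comparisons.** The procedure is the three-arm test first, then Holm over three pairs (0.0167, 0.025, 0.05), by exact enumeration at the undiluted rates.

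| Comparison | Power |
|---|---|
| 700 mg v placebo | 93.7% |
| 420 mg v placebo | 63.5% |
| Both doses v placebo | 62.7% |
| 420 mg v 700 mg | 23.6% |

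**The case against.** The strongest reply is that the error is harmless. The stated figure is below the true power of the primary test, so 120 patients are more than enough for the hypothesis as written. No test, alpha, endpoint or sample size has to change. This stands, and it limits the point to correcting a stated figure.

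A second reply is that 83% may include a silent allowance for dropouts, since about 18% to 19% failures in every arm would produce it. The text does not say so: the figure is attached to the undiluted rates and no dropout rate appears. The reply does show that 93% to 95% should not be inserted without stating the dropout assumption.

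A reader might infer that the 83% conceals a weakness in the 420 mg comparison, or overstates its power. The protocol does not support that. Section 6.3 attaches the figure to the null hypothesis, which section 6.2 defines across all three arms. Neither section applies it to a single dose. Pairwise power is not a declared target, and the pairwise tests are follow-ups in a phase II trial. Leaving pairwise power out is therefore not an error.

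A reader might also conclude that the 83% came from a two-arm comparison of 15% with 47.5% at alpha 0.025. The match is exact to the decimal and the 47.5% is in the text, but the protocol states alpha 0.05 and other routes come close. The source is possible but unproven, and the finding does not depend on it.

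**Conclusion.** The point holds as a moderate correction. On the protocol's own inputs the planned test has 92.9% power (asymptotic) or 95.3% (exact), and 83% lies outside what the choice of approximation can explain. The reproduction of the 12% safety power supports the method.

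The conclusion assumes that the null hypothesis in section 6.3 is the primary one in section 6.2, the only primary efficacy null the protocol defines, and that the assumed rates are the rates as analysed, with dropouts already counted as failures. If they are not, the correct figure depends on a dropout rate that the protocol does not give: about 88% at 10% and 82% at 20%.

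The documents do not support a claim that the trial is too small for its primary hypothesis at the stated rates.

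**What to change.** In section 6.3:

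1. Name the test behind the power statement: the three-arm chi-square test of section 6.2, 2 df, alpha 0.05.
2. Replace 83% with about 93% (noncentral chi-square) or 95% (exact), naming the method.
3. State whether the 15%, 40% and 55% already count patients without a follow-up biopsy as failures. If not, state the assumed dropout rate and give the power after dilution.
4. If 83% was meant for a different calculation, say which one, with its groups and alpha.

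As an optional addition, give power under the three-arm test followed by Holm: about 94% for 700 mg against placebo, 63% for 420 mg against placebo and 24% for 420 mg against 700 mg. This keeps the single overall figure from being read as applying to each dose. The 47.5% average may stay as description if it is clear that the planned test does not use it.

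The cost is protocol wording only, with no change to N, design or conduct. If pairwise power is added, the modest figure for 420 mg becomes visible.
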